## METHODS

### Study design and location

This multicenter, multinational, cohort study protocol will include patients with ARF transitioning to spontaneous ventilation in ICUs in Latin American countries.

We will invite investigators from ICUs in ten Latin American countries. Invitations will be sent to all ICUs in the Brazilian Research in Intensive Care Network (BRICNet) and Latin American Intensive Care Network (LIVEN) databases by email, and we have identified one investigator in each of the countries to serve as a national coordinator responsible for using a snowball strategy to invite ICUs and support the local investigators with regulatory and logistic issues.

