### Objectives and outcomes

The primary objectives are to estimate the prevalence of low V_T_ ventilation (V_T_ < 8mL/kg of PBW) in the first 24 hours of spontaneous ventilation in patients with hypoxemic ARF and its association with ventilator-free days on day 28. Tidal volume will be assessed five times over the first 24 hours after the transition to spontaneous ventilation to account for potential variation. To determine whether V_T_ was below or above 8 mL/kg of PBW for a given patient, we will calculate the weighted average V_T_ based on the duration of each evaluation period. Accordingly, the first assessment, collected one hour after the transition, carries a weight of 1/24, the second assessment, collected 5 hours after (and 6 hours after the transition), carries a weight of 5/24, and the third, fourth and fifth assessments, collected after 12 hours, 18 hours and 24 hours of the transition, respectively, will each carry a weight of 6/24.

The secondary objectives are to estimate the association between the rate of adherence to low V_T_ ventilation in spontaneous ventilation and survival, estimate the incidence of asynchrony in the first 24 hours after the transition to spontaneous ventilation and associated mortality, estimate the proportion of patients who returned to sedation and controlled MV in the first 24 hours or at any time after the transition to spontaneous ventilation, assess the adherence to low positive end-expiratory pressure (PEEP) by fraction of inspired oxygen (FiO_2_) table in the first 24 hours after the transition to spontaneous ventilation, and identify barriers associated with nonadherence to low V_T_ ventilation during spontaneous ventilation.

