### Sample size calculation

There are no previous studies that have estimated the rate of adherence to low V_T_ in patients with spontaneous ventilation; therefore, we used a conservative approach. To estimate the prevalence with a confidence limit of 5% precision, an anticipated adherence of 50%, and up to 10% loss to follow-up, we estimated that we need to include 422 patients. Additionally, we calculated the power to detect a 3 day difference in ventilator-free days with a standard deviation of 9 days,^(22)^ and we anticipate a statistical power of at least 80% even with a loss to follow-up rate of 10%, provided that the prevalence is between 25 and 75%.

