The comparison of V_T_ during the initial 24 hours of spontaneous ventilation (less than 8mL/kg of PBW versus greater than 8mL/kg) in relation to ventilator-free days within 28 days will be performed using mixed generalized regression models considering the distribution that best fits the data, incorporating center as a random effect. We constructed a conceptual causal diagram in the format of a directed acyclic graph (DAG),^(24)^ including the association between V_T_ during the first 24 hours of spontaneous ventilation and ventilator-free days at 28 days and the most relevant variables (Figure 1S - Supplementary Material): body mass index (BMI) and SAPS 3 at baseline, SOFA on the day before transition, PaO_2_/FiO_2_ at the moment of the ARF diagnosis, and PEEP, RASS, and pH one hour before transition.

All analyses will be performed using the R statistical program (R Core Team; Vienna, Austria; https://www.R-project.org), and we will consider p < 0.05 to indicate statistical significance.

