The multicenter and multinational characteristics of our study, with the participation of ten Latin American countries, add significant diversity to the population of patients included and allow a more comprehensive understanding of regional variations in clinical practices. This observational study will reflect real-life clinical scenarios, and the findings will be derived from routine patient care settings, increasing the practical relevance of the results. This study has the potential to influence clinical decision-making, inform future clinical trials, and ultimately improve patient outcomes.

Our study has some limitations. We will collect detailed data regarding ventilatory parameters only for the first 24 hours of the transition to spontaneous ventilation, and we recognize that these first 24 hours are not necessarily representative of the remaining days in MV; in addition, patients can only be included once in the study because survival is one of the secondary outcomes; therefore, we will only collect data for the first transition. The tidal volume will not be obtained continuously but rather will be collected at several timepoints during the first 24 hours of spontaneous ventilation. To better represent these variations, we will calculate the weighted average of the V_T_ based on the duration of each evaluation period. This method takes into account changes in V_T_ over a 24-hour period, assigning different weights to each data point.

The participating ICUs in the study were invited using the databases of large research networks, and it is possible that the investigators in the ICUs had more knowledge and experience with MV than did the average Latin American ICU practitioners, which could generate selection bias and restrict the external validity of the study. However, invitations were sent to a large number of ICUs regardless of research experience, and we did not restrict participation to active network members. Although the multinational approach increases external validity, the specific regional characteristics of Latin American ICUs may limit the generalizability of the results to countries in other parts of the world.

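### A random centre effect alone may leave residual confounding by ICU in the tidal volume coefficient; a prespecified within-between version of the models is a cheap safeguard

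*Protocol article*

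**What the plan says.** Under Objectives and outcomes, the association of low VT with ventilator-free days at day 28 is one of two primary objectives. Exposure is classified per patient from repeated readings: "we will calculate the weighted average V_T_ based on the duration of each evaluation period". It is observed, not allocated.

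Statistical plan analysis specifies the model for that association as "mixed generalized regression models considering the distribution that best fits the data, incorporating center as a random effect". The 28-day mortality analysis is a mixed logistic regression that treats centre in the same way. The variables named for the causal diagram are BMI and SAPS 3 at baseline, followed by "SOFA on the day before transition, PaO_2_/FiO_2_ at the moment of the ARF diagnosis, and PEEP, RASS, and pH one hour before transition". All describe the patient. The text mentions no centre mean of VT, fixed centre effect, country term or ICU-level covariate.

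On sites, Study design and location has national coordinators "responsible for using a snowball strategy to invite ICUs". The number of ICUs is not given. The Discussion says the ten-country design will "allow a more comprehensive understanding of regional variations in clinical practices". It also accepts that participating investigators may know more about ventilation than the average practitioner, but treats this as a matter of selection and external validity.

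**The concern.** A random-intercept coefficient is a weighted mixture of two contrasts: low-VT against other patients inside the same ICU, and ICUs with much low VT against ICUs with little. The mixture is unbiased for the within-ICU association only if the centre effect is unrelated to centre exposure. Randomisation within centres would secure that; an observed practice does not.

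ICUs that keep VT low may also differ in staffing and weaning habits, which can change ventilator-free days and which the listed patient-level variables do not measure. Part of such a difference could then appear in the VT coefficient even if VT had no effect inside any ICU. At stake is the interpretation of a primary result that the article supports with a causal diagram and hopes will inform practice and later trials.

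**Working it through.** **1. The plan's own figures.** They reproduce and are not in dispute.
- The article states "we estimated that we need to include 422 patients", "with a confidence limit of 5% precision, an anticipated adherence of 50%, and up to 10% loss to follow-up". 1.96² × 0.5 × 0.5 / 0.05² = 384, and 384 × 1.10 = 422.
- It also states "power to detect a 3 day difference in ventilator-free days with a standard deviation of 9 days". Evaluable patients: 422 × 0.90 ≈ 380. SE = 9 × √(1/n₁ + 1/n₂), and power = Φ(3/SE − 1.96).
- 50% prevalence (190/190): SE = 0.923, power 90.1%. 25% or 75% (95/285): SE = 1.066, power 80.3%.

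**2. How much a random intercept removes.** With m patients per ICU, the between-ICU contrast is down-weighted by λ = 1/(1 + m × ICC/(1 − ICC)). At an assumed ICC of 0.10:
- 20 ICUs, m = 19: λ = 1/(1 + 19 × 0.111) = 0.32
- 40 ICUs, m = 9.5: λ = 0.49
- 80 ICUs, m = 4.75: λ = 0.65

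The random effect therefore removes part of the between-ICU difference, and least when ICUs are many and small.

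**3. Simulation with a true effect of zero.** 380 patients, SD 9 days, 50% low VT, Gaussian outcome, no covariates. The article gives no number of ICUs, ICC, spread of adherence between ICUs, or correlation between ICU practice and ICU outcome, so all four are assumptions.

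*Set A:* 20, 40 or 80 ICUs; outcome ICC 5–10%; adherence SD 1 on the logit scale; random intercept only.

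| Practice–outcome correlation | Spurious difference (days) | Type I error |
|---|---|---|
| 0 | 0 | nominal |
| 0.25 | about 0.2–0.45 | about 4–7% |
| 0.5–0.8 | about 0.4–1.4 | about 7–33% |

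Check by normal approximation, with shift = bias/0.923 and type I error = Φ(−1.96 + shift) + Φ(−1.96 − shift): 0.2 days gives 5.5%, 0.45 gives 7.8%, 0.4 gives 7.2%, 1.4 gives 33%. The middle row is best read as reaching about 8% at its upper end.

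*Set B:* REML fit, 600 data sets per scenario, outcome ICC 0.05–0.20, latent exposure ICC 0.10–0.30, correlation 0, 0.5 or 1. Selected rows, bias in days:

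| ICUs | ICC outcome/exposure | Correlation | Crude | Random intercept | Centre proportion added | Type I error, without → with |
|---|---|---|---|---|---|---|
| 20 | 0.10/0.20 | 0.5 | 0.95 | 0.34 | −0.02 | 7% → 5% |
| 40 | 0.10/0.20 | 0.5 | 1.05 | 0.58 | 0.00 | 11% → 4% |
| 80 | 0.10/0.20 | 0.5 | 1.03 | 0.78 | 0.05 | 14% → 4% |
| 80 | 0.20/0.30 | 1 | 3.49 | 2.22 | 0.04 | 68% → 5% |

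The share of crude bias left in the first three rows is 0.34/0.95 = 0.36, 0.58/1.05 = 0.55 and 0.78/1.03 = 0.76, in line with the pattern of λ. Over all Set B scenarios with non-zero correlation it runs from 18% (0.29/1.61) to 84% (0.415/0.493). At correlation 0, the random-intercept bias lies between −0.01 and 0.08 days (simulation error about 0.93/√600 = 0.04) and type I error is 4–6%. With the centre proportion added, bias stays within ±0.08 days and type I error is 4–7% throughout.

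**4. Price in precision.** Under Set A assumptions the within-centre SE is about 4–8% larger with 20 ICUs, 8–11% with 40 and 16–20% with 80. Over the whole range, assuming the inflation carries over to other prevalences:
- 50% prevalence: SE 0.960 to 1.108; Φ(3/0.960 − 1.96) = 88%, Φ(3/1.108 − 1.96) = 77%.
- 25% or 75%: SE 1.109 to 1.279; power 77% down to 65%.

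**The case against.** A random centre effect is a conventional choice and contradicts nothing in the article. Several further points stand.

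- A reader might infer that a random effect only repairs the standard error, so that ICU differences pass wholesale into the VT estimate. They do not: it removes part of the difference, and nothing needs removing if ICU practice and outcome are unrelated.
- A reader might take 33% as the false-positive rate of the planned analysis. It is the upper end of an assumed range, without covariates. RASS, SAPS 3, SOFA and PaO2/FiO2 bear on sedation and case mix and, if adjusted for, may absorb some of the confounding. They do not capture staffing or weaning habits.
- The article does not say that low-VT ICUs have better outcomes. It says only that practice is expected to vary. The snowball invitation makes small centres plausible but shows no link between exposure and outcome.
- The Introduction and Discussion note that spontaneous VT also depends on the patient's drive and effort. Much of the variation may lie within centres, and the within-centre contrast can itself be confounded by drive. It is free of confounding by stable ICU characteristics, not of all bias.
- The article says random effect, not random intercept, and the causal diagram (Figure 1S) is not shown. The intercept is the usual reading, but it is a reading.

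These points limit the size and certainty of the concern. They do not remove the mechanism: the article fixes how centre enters a primary analysis of an unallocated exposure, and no stated term separates the two contrasts.

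**Conclusion.** The point holds as a cheap improvement, not as an error. The models for ventilator-free days and 28-day mortality may leave residual confounding by ICU in the VT coefficient. Its size cannot be read from the article. On the Set A assumptions it runs from zero to about 1.4 ventilator-free days as the assumed practice–outcome correlation goes from 0 to 0.8, before any reduction by the listed covariates. Real ventilator-free days are bounded and have many zeros, which would change these figures but not the mechanism.

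A reader might go further and conclude that the sample size or power statement is wrong, or that the planned estimate must be replaced. The documents support neither. The 422 patients and the 80% both reproduce for the comparison as planned, and making the within-centre estimate primary is a trade-off against power.

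**What to change.** Prespecify a within-between version of both models: keep the random centre effect and add each centre's proportion of low-VT patients as a covariate. Report the patient-level (within-centre) and the between-centre coefficients separately, and state in advance that the association will not be interpreted as a VT effect if it is not supported within centres. This can stand as a key sensitivity analysis beside the planned model.

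It costs one derived covariate from data already collected. As a sensitivity analysis it leaves the power statement for the planned model untouched. If the within-centre coefficient were made primary, its larger standard error would take power below the stated 80% at 25% or 75% prevalence in every scenario examined, and at 50% prevalence towards the 80-ICU end. The power statement in Sample size calculation would then have to be restated with the expected number of ICUs.

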## Abstract

**Objective::**

Patients with acute respiratory failure often require mechanical ventilation to reduce the work of breathing and improve gas exchange; however, this may exacerbate lung injury. Protective ventilation strategies, characterized by low tidal volumes (≤ 8mL/kg of predicted body weight) and limited plateau pressure below 30cmH_2_O, have shown improved outcomes in patients with acute respiratory distress syndrome. However, in the transition to spontaneous ventilation, it can be challenging to maintain tidal volume within protective levels, and it is unclear whether low tidal volumes during spontaneous ventilation impact patient outcomes. We developed a study protocol to estimate the prevalence of low tidal volume ventilation in the first 24 hours of spontaneous ventilation in patients with hypoxemic acute respiratory failure and its association with ventilator-free days and survival.

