### Study measures and data collection

The following baseline characteristics related to admission to the ICU and initiation of MV will be obtained from the patient's medical records: age, sex, height (assessed using a tape measure with the patient in the supine position), weight reported by the ICU team, main reason for admission to the ICU, cause of ARF, arterial oxygen pressure/fraction of inspired oxygen ratio (PaO_2_/FiO_2_) on the day of the ARF diagnosis, date of intubation, risk factors for ARDS, comorbidities (cardiac, respiratory, neurological, renal, hepatic, immunosuppression, cancer, arterial hypertension, diabetes and smoking) and Simplified Acute Physiology Score 3 (SAPS 3). We will calculate the PBW according to the following formulas:

$$\begin{array}{c} 50+0.91\times \left(\text{height in centimeters}-\;152.4\right)\text{for males}\\ 45.5+0.91\times \left(\text{height in centimeters}-\;152.4\right)\text{for females} \end{array}$$

We will also retrospectively collect the ventilatory parameters from the day before inclusion in the study from the patient's medical records, in addition to the use of vasopressors, sedatives, neuromuscular blockers and analgesics, ARDS diagnosis, Richmond Agitation-Sedation Scale (RASS) score, presence of *delirium* assessed by the Confusion Assessment Method in an Intensive Care Unit (CAM-ICU) scale or clinical assessment, Sepsis-related Organ Failure (SOFA) score, blood gas analysis and other laboratory data for diagnosing organ failure. We will also calculate the respiratory system compliance and resistance from the day before study enrollment (for patients under deep sedation and/or neuromuscular blockage). The main study measures and data collection methods are shown in table 2.

**Table 2 t2:** Characteristics of the study population

Characteristic		Value
Age (years)		xx ± x
Male, n (%)		n (xx)
BMI (kg/m^2^)		xx ± x
SAPS 3 score		xx ± x
SOFA		xx (xx - xx)
LIP score		xx (xx - xx)
Charlson index		xx (xx - xx)
Cause ARF		
	Pneumonia (bacterial, viral, opportunistic)	n (xx)
	Extrapulmonary sepsis	n (xx)
	Coma/lowered level of consciousness	n (xx)
	Cardiogenic pulmonary edema/heart failure	n (xx)
	Aspiration	n (xx)
	Hypovolemic shock	n (xx)
	Others	n (xx)
Days of intubation prior to inclusion		xx (xx - xx)
Cause of hospitalization		
	Acute respiratory failure	n (xx)
	Sepsis	n (xx)
	Neurologic diseases	n (xx)
	Postoperative monitoring	n (xx)
PaO_2_/FiO_2_ ratio at ARF diagnosis		xx ± x

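### The variables named for the primary tidal volume and ventilator-free-days analysis leave out ARDS diagnosis and cause of respiratory failure, both recorded before exposure, so residual confounding by diagnosis remains possible

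*Protocol article*

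**What the plan says.** Under Objectives and outcomes, the protocol article makes two things primary: how common low VT is over the first day of spontaneous breathing, studied "in patients with hypoxemic ARF and its association with ventilator-free days on day 28". The Statistical plan analysis section says the comparison of ventilator-free days between VT groups will use "mixed generalized regression models considering the distribution that best fits the data, incorporating center as a random effect". It then describes a causal diagram, placed in supplementary Figure 1S, and spells out the variables it treats as most relevant. The first four are "body mass index (BMI) and SAPS 3 at baseline, SOFA on the day before transition, PaO_2_/FiO_2_ at the moment of the ARF diagnosis". The other three, taken an hour ahead of the transition, are PEEP, RASS and pH. That makes seven variables. Neither ARDS diagnosis nor cause of ARF is among them, and no reason is given.

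Both are collected. Under Study measures and data collection, the baseline record includes "main reason for admission to the ICU, cause of ARF, arterial oxygen pressure/fraction of inspired oxygen ratio". The data taken from the day before inclusion cover ventilatory parameters "in addition to the use of vasopressors, sedatives, neuromuscular blockers and analgesics, ARDS diagnosis, Richmond Agitation-Sedation Scale (RASS) score". Table 2 gives the expected causes of ARF, which run from pneumonia and aspiration to cardiogenic edema, hypovolemic shock and "Coma/lowered level of consciousness".

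**The concern.** A confounder here must bear on the VT a patient receives and on the time to liberation or death. The article gives grounds for the first link. Its abstract says that protective strategies "have shown improved outcomes in patients with acute respiratory distress syndrome", and the Introduction rests the case for low VT on the same population, so clinicians may hold VT down more firmly in ARDS than in other causes of hypoxemia. The Introduction also says that acute lung injury can raise respiratory drive and so raise VT, which is the opposite direction. The exclusion criteria in Table 1 remove severe central nervous system injury where drive makes a protective VT unattainable, which concedes that etiology shapes VT. The Discussion cites physiological studies of VT during this transition specifically in ARDS.

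The second link is plausible on general grounds: ventilation time and death, which together make up ventilator-free days, are likely to differ between ARDS, cardiogenic edema and coma.

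If both links hold after adjustment for the seven variables, the VT coefficient carries part of the effect of diagnosis. Should ARDS patients be kept at low VT more often and do worse, low VT looks harmful or a benefit is masked. Should they breathe larger volumes and do worse, low VT looks better than it is.

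**Working it through.** **The text.** Of the pre-exposure data, seven variables are named for the diagram. ARDS diagnosis (day before inclusion) and cause of ARF (baseline) are recorded and not named. Both precede the exposure, which is VT after transition, so adjusting for them does not adjust away an effect of VT.

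**The plan's own figures.** Inputs from Sample size calculation: precision 5%, anticipated prevalence 50%, loss 10%, difference 3 days, SD 9 days. Two-sided 5% is assumed, as sidedness is not stated.

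- Sample size: 1.96² × 0.5 × 0.5 / 0.05² = 384.1, and 384.1 × 1.1 = 422.6. The plan says 422.
- Evaluable after 10% loss: 422 × 0.9 = 379.8.
- Standard error of the difference at prevalence p: 9 × √(1/(379.8p) + 1/(379.8(1 − p))). This is 1.07 days at p = 25% or 75%, and 0.92 days at 50%.
- Power for 3 days, Φ(3/SE − 1.96): 80.3% at 25% or 75%, and 90.1% at 50%. The plan's claim of at least 80% reproduces. It is an unadjusted two-group calculation and does not bear on confounding.

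**Illustrative size of the bias.** The article gives no ARDS share, imbalance or effect, so these inputs are assumptions. For a difference in means, one omitted binary confounder gives

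bias = (difference in ventilator-free days by ARDS) × (difference in ARDS frequency between VT groups),

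with both factors taken after adjustment for the seven listed variables.

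| Outcome difference | Remaining imbalance | Bias (days) | Share of 3 days |
|---|---|---|---|
| 2 days | 10 points | 0.2 | 7% |
| 3 days | 20 points | 0.6 | 20% |
| 4 days | 30 points | 1.2 | 40% |

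With no true VT effect, the chance of p < 0.05 is Φ(b/SE − 1.96) + Φ(−b/SE − 1.96). A bias b of 0.6 days gives 8.7% at 25% prevalence and 10.0% at 50%. A bias of 1.2 days gives 20.3% and 25.5%.

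**Cost of adding the terms.** If they explain a share R² of VT group and give no gain in residual variance, the standard error is divided by √(1 − R²).

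| R² | Power at 25% or 75% | Power at 50% |
|---|---|---|
| 0 | 80.3% | 90.1% |
| 2% | 79.5% | 89.5% |
| 5% | 78.3% | 88.6% |
| 10% | 76.1% | 86.9% |

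**The case against.** The strongest reply is that the evidence is incomplete. Figure 1S is not shown. The text calls its list the most relevant variables, and does not say that it holds every node or that it is the model's adjustment set. A diagram can contain ARDS and still not require adjustment for it, if its paths to VT run through listed variables. This stands. A reader might infer that the primary model certainly omits diagnosis, and the document does not establish that. What it does establish is that the article chose to spell out a set, that diagnosis is not in it, and that no argument is given that the set blocks the paths.

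The listed variables also do some of the work. PEEP may carry part of how ARDS is managed, RASS bears on the coma category, and PaO2/FiO2 and pH add something. A reader might infer that PaO2/FiO2 is uninformative because all patients are at or below 300. That does not follow, because an upper limit leaves variation beneath it. Still, none of the seven identifies the cause of the hypoxemia, and a random center effect does not remove differences in diagnosis between patients of the same center. The issue is residual confounding, not absence of adjustment.

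The indication itself may be weak in this phase. The Discussion says VT is hard to control during spontaneous ventilation, and the Introduction reports low adherence despite the ARDS evidence. This also stands, and it is one reason why neither sign nor size can be claimed. At the low end, 0.2 days is about a fifth of a standard error (0.2/0.92).

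Finally, it is tempting to ask for a VT-by-ARDS interaction. With half the cohort in ARDS and half at low VT, there are four cells of about 95 patients. The standard error is 9 × √(4/95) = 1.85 days, and 80% power would need an interaction of about 2.8 × 1.85 = 5.2 days, well above the 3-day target. It is not recommended.

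**Conclusion.** The concern holds as one of possible residual confounding in a primary association. Two recorded, pre-exposure variables that the article itself connects to achieved VT are absent from the set it names, and the named variables replace them only in part. The sign is unknown, and a claim that the analysis is biased against low VT, or in its favor, would go beyond the documents. The 0.2 to 1.2 day range is an illustration. It assumes a 10 to 30 point imbalance that survives adjustment and a 2 to 4 day outcome difference, and it treats the effect as a difference in means although the model's distribution is still open. Since the proxies would absorb some of any raw imbalance, the true figure is probably smaller. The change is still worth making because its cost is low and the association is a stated primary objective.

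**What to change.** Add ARDS diagnosis on the day before inclusion, and cause of ARF with the Table 2 categories merged into a few groups, to the causal diagram and to the ventilator-free-days model. State that the resulting list is the adjustment set. Report the VT estimate with and without the two variables, so that readers can see how much diagnosis moves it.

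This changes analysis wording only, as both variables are already collected. Table 2 has seven causes, so unmerged they would add six terms plus one for ARDS. Merging into three groups, for example, would bring the total to three. The interval widens slightly. At the ends of the prevalence range, power could fall a little below the stated 80%, as the working shows, unless the added terms also explain outcome variance, which would offset some of the loss.

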### One hour before transition

The following data on controlled ventilation will be recorded retrospectively: ventilatory mode; programmed respiratory rate; patient's total respiratory rate; minute ventilation; peak airway pressure; V_T_; and PEEP. We will also collect vital data (heart rate, mean arterial pressure, peripheral oxygen saturation), arterial blood gas analysis data (obtained as close as possible to the collection of ventilatory data will be recorded), the presence of major asynchronies,^(23)^ the use of vasopressors, the use of sedatives and analgesics, the RASS score, the presence of *delirium* assessed by the CAM-ICU scale or clinical assessment.

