## DISCUSSION

The SPIRAL study was developed to describe the ventilation of patients with ARF in spontaneous ventilation, mainly with respect to the V_T_ applied in this phase. Randomized clinical trials have shown that low V_T_ and limited plateau pressure during controlled ventilation reduce mortality and ventilator-induced lung injury,^(3,7)^ and clinical practice guidelines recommend using protective ventilation, defined as a V_T_ of 4 - 8mL/kg and a plateau pressure below 30cmH_2_O.^(2,26)^ However, in spontaneous ventilation, the V_T_ varies according to the adjusted level of inspiratory assistance and the patient's inspiratory effort, which makes it difficult to control the V_T_. Previous physiological studies^(27,28)^ have shown that it is possible to maintain V_T_ below 8mL/kg of PBW in the majority of patients diagnosed with ARDS who are transitioning to spontaneous ventilation. The study's focus on adherence to low V_T_ during spontaneous ventilation reflects challenges faced by clinicians in daily practice. We chose to use a cutoff of 8mL/kg PBW instead of 6mL/kg because although most clinical randomized trials have targeted 6mL/kg PBW, V_T_ up to 8mL/kg were allowed in most studies.^(4,7)^ Additionally, clinical guidelines define protective ventilation as a V_T_ of 4 - 8 mL/kg^(2,26)^ and prior observational trials^(19)^ have used this definition.

The study's primary and secondary objectives cover a broad spectrum of clinical outcomes, including ventilator-free days, survival, incidence of asynchrony, and identification of potential barriers to adherence to low V_T_, enabling a comprehensive view of the impact of ventilation strategies on patient-centered outcomes. Data will be collected at several timepoints during the first 24 hours after the transition to spontaneous ventilation. This approach takes into account possible variations over time and will enable a differentiated understanding of V_T_ dynamics during this critical period. Due to possible variations in V_T_ with spontaneous ventilation over time, we chose to use the weighted average of V_T_ to obtain a more representative assessment of the ventilation dynamics during the first 24 hours of spontaneous ventilation.

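### Tidal volume one hour before transition is collected but is not among the causal-diagram variables listed for the ventilator-free-days association, so carry-over from the controlled phase may be left unadjusted

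*Protocol article*

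**What the plan says.** The Abstract gives the gap to be filled: "it is unclear whether low tidal volumes during spontaneous ventilation impact patient outcomes". Under Statistical plan analysis, the comparison of V_T groups "in relation to ventilator-free days within 28 days will be performed using mixed generalized regression models", with centre as a random effect. The same paragraph describes a directed acyclic graph (DAG) that holds this association "and the most relevant variables (Figure 1S - Supplementary Material"). The variables named are "body mass index (BMI) and SAPS 3 at baseline, SOFA on the day before transition", then "PaO_2_/FiO_2_ at the moment of the ARF diagnosis, and PEEP, RASS, and pH one hour before transition".

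The section One hour before transition records, for controlled ventilation, "ventilatory mode; programmed respiratory rate; patient's total respiratory rate; minute ventilation; peak airway pressure; V_T_; and PEEP". Table 3 gives V_T per kg of predicted body weight a column for one hour before. V_T and PEEP therefore come from the same record, but only PEEP is in the list.

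The Discussion states: "Randomized clinical trials have shown that low V_T_ and limited plateau pressure during controlled ventilation reduce mortality and ventilator-induced lung injury". Its limitations paragraphs do not mention V_T before transition.

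**The concern.** All patients are enrolled from controlled ventilation, so V_T in that phase comes before the exposure. The article's own premise is that it affects outcome, and because death before day 28 scores zero ventilator-free days (Follow-up), an effect on mortality enters the primary outcome directly. It is also plausible that a patient with low V_T under control has low V_T just after transition: the lungs, the respiratory drive and the treating team are the same. A variable that precedes the exposure, predicts it and affects the outcome is a confounder.

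If it is left out, some of the benefit of protective ventilation in the controlled phase would be attributed to the spontaneous phase. With positive carry-over and a beneficial controlled-phase effect, the bias favours low V_T. The centre random effect does not remove carry-over between patients of the same centre, and none of the listed variables is itself a measure of V_T.

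**Working it through.** **1. The plan's own power figure.** Inputs from Sample size calculation: 422 patients, 10% loss, a 3-day difference, SD 9 days, prevalence 25% to 75%. The 5% significance level is from Statistical plan analysis; two-sided is assumed. Evaluable patients: 422 × 0.9 ≈ 380.

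- 25% or 75% prevalence (95 against 285): SE = 9 × √(1/95 + 1/285) = 1.066; 3/1.066 − 1.96 = 0.854; power 80.3%.
- 50% prevalence (190 against 190): SE = 9 × √(2/190) = 0.923; power 90.1%.

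The stated power of at least 80% is reproduced, with almost no reserve at the ends of the range.

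**2. Possible size of the carry-over.** The documents give none of these inputs; all are assumptions.

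- pc, share of patients with low V_T under control: 0.60 to 0.80
- a, chance of low V_T after transition if it was low before: 0.60 to 0.65
- b, the same chance if it was not low before: 0.25 to 0.40
- g, effect of low controlled-phase V_T on ventilator-free days: 2 to 3 days

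P = pc·a + (1 − pc)·b is the share with low V_T after transition. The imbalance in low controlled-phase V_T between the two exposure groups is pc·a/P − pc·(1 − a)/(1 − P), and the spurious difference is g times that.

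| | pc | a | b | P | Imbalance | g | Spurious difference |
|---|---|---|---|---|---|---|---|
| Low end | 0.80 | 0.60 | 0.40 | 0.56 | 0.857 − 0.727 = 0.130 | 2 | 0.26 days |
| High end | 0.60 | 0.65 | 0.25 | 0.49 | 0.796 − 0.412 = 0.384 | 3 | 1.15 days |

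Against the 3-day difference this is 0.26/3 ≈ 9% to 1.15/3 ≈ 38%. A wider set of assumptions (effect 1 to 3 days, imbalance 0.1 to 0.5) gives 0.1 to 1.5 days.

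With near-equal groups (SE 0.923), the chance of p < 0.05 when the spontaneous phase has no effect would be about 6% at the low end and 24% at the high end, instead of 5%. This is a linear approximation that gives no credit to the other covariates.

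**3. What adjustment costs in power.** Let r be the correlation between the low-V_T exposure and pre-transition V_T (assumed). With no gain in residual variance, the effective sample is 380 × (1 − r²).

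| r | Power, 25/75 split | Power, 50/50 split |
|---|---|---|
| 0 | 80.3% | 90.1% |
| 0.3 | 76.5% | 87.3% |
| 0.5 | 68.3% | 80.3% |
| 0.7 | 52.0% | 64.1% |

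At a 25/75 split, power falls below 80% from about r = 0.1. With both V_T variables taken as binary, the scenarios in step 2 imply r of about 0.16 to 0.39.

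**The case against.** The strongest reply is that the text never calls the list the adjustment set. It describes the main variables of a diagram placed in a supplement that is not shown, and a separate analysis plan may exist. Pre-transition V_T may be in either. This stands, and it makes the point conditional. The point does not vanish, because the article names the causal variables, takes PEEP, RASS and pH from the same hour, and passes over the earlier value of the exposure itself.

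Second, the carry-over is not documented. The Discussion says that spontaneous V_T depends on the level of assistance and on the patient's effort, which may weaken the link with the controlled phase. This also stands: the documents give no correlation.

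Third, the assumed 2 to 3 days may be generous. Ventilator-free days are counted from inclusion, and only patients who reach transition are enrolled, so deaths and ventilator days before transition lie outside the outcome. Severity scores, PaO_2_/FiO_2_, PEEP, RASS, pH and centre may also block part of the path. Both are reasons to read the range in days as illustrative.

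A reader might go further and infer that the design cannot separate the two phases, or that a positive result could not be read as evidence about spontaneous ventilation. The documents support neither. The measurement needed is collected. And if 3 days were observed, the assumed bias would still leave 3 − 1.15 = 1.85 to 3 − 0.26 = 2.74 days.

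**Conclusion.** The point holds as a correctable gap in the stated causal model. V_T one hour before transition is collected and tabulated, is absent from the listed variables, and is a plausible confounder on the article's own premises. If the list is the adjustment set, part of any association with ventilator-free days may belong to the controlled phase: about 0.3 to 1.2 days under the assumed inputs, before allowing for the other listed covariates, against a 3-day target. That is partial confounding of a primary objective. The size rests wholly on assumptions about carry-over and the controlled-phase effect, and whether the omission carries into the final model cannot be settled from the text shown. The sample size of 422 is not called into question.

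**What to change.** Add V_T one hour before transition, in mL/kg of predicted body weight and as a continuous term, to the DAG and to the adjusted ventilator-free-days model. If power is the worry, at least pre-specify a sensitivity analysis that reports the V_T effect with and without this term. If the supplement or analysis plan already includes it, align the article's list; if it was left out on purpose, give the reason.

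No new data are needed. The price is a wider interval: at 25% or 75% prevalence, power goes from 80.3% to 76.5% if the correlation is 0.3 (assumed), and further down if it is higher. A single reading stands in imperfectly for the whole controlled phase, so adjustment reduces the carry-over but may not remove it; the report should say so.
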